### 3.3 SECONDARY END POINTS

- Single components of the primary outcome
- Episodes of infection and graft rejection defined by the treating medical personnel
- Severe infection (necessitating treatment in the inpatient or day-care ward) and severe rejection (excluding BL TCMR)
- All of the three mentioned secondary end-points including COVID-19
- Episodes of infection due to COVID-19
- Estimated glomerular filtration rate (eGFR; current CKD EPI and MDRD abbreviated)
- Rejection detected by protocol biopsy at month 12 post-transplantation: according to BANFF 2019 meeting report (including/excluding BL TCMR) and according to molecular microscope (MMDX)
- *de novo* donor specific antibodies (DSA)

- Plasma TTV load
- TAC trough level and dose
- Unchanged, increased, and decreased TAC trough target levels
- Health related quality of life: SF-36 and MTSOSD-59R questionnaires
- Drug adherence assessed according to paper-based assessment, MEMS® Buttons (AARDEX Group, Switzerland) on TAC blisters, BAASIS questionnaire, claimed prescriptions, psychological evaluation and TAC trough level variability
- Adverse Events and Serious Adverse Events (AEs/SAEs)
- Development of malignoma

### 3.4 INVESTIGATIONS ACCOMPANYING THE TRIAL

**Sub-study:** Further immunologic monitoring; Biological material (serum, plasma, whole blood and urine) will be sampled for further immunologic monitoring including but not restricted to further DSA assessment, donor derived cell free DNA [ddcfDNA], gene expression and urinary TTV and chemokines.

### 3.5 SAMPLE SIZE

**A total of 260 patients will be included in the trial, 130 of them in the active group and 130 in the control group.**

For the sample size calculation, we analysed the occurrence of the primary endpoint (infection, allograft rejection, death and graft loss) in recipients of a kidney allograft transplanted between 1.1.2012 and 31.12.2018 at the Vienna centre, applying the trial-specific inclusion and exclusion criteria (unpublished data). Overall, 40% of patients experienced the primary endpoint between month 3 and 12 after transplantation.

An inclusion of 260 recipients will give a power of >90% to demonstrate non-inferiority with respect to the primary endpoint (assuming a decrease from 40% to 30%) using a one-side significance level of alpha 2.5%, given a 1:1 randomisation ratio. If the differences are larger, there is also sufficient power to demonstrate superiority. More details are given in section 10.

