#### Superiority hypothesis:

If non-inferiority is reached, the study will demonstrate superiority of TTV-guided immunosuppression (arm T) compared to standard dosing (arm S) in the same endpoint by testing the hypothesis:

$$H_0: p_T - p_S \geq 0 \text{ versus } H_1: p_T - p_S < 0$$

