### 10.2 SAMPLE SIZE CALCULATION

For the sample size calculation, we analysed the occurrence of the primary endpoint (infection, allograft rejection, death and graft loss) in recipients of a kidney allograft transplanted between 1.1.2012 and 31.12.2018 at the Vienna centre, applying the trial-specific inclusion and exclusion criteria (unpublished data). Overall, 40% of patients experienced the primary endpoint between month 3 and 12 after transplantation. Therefore, we assume a composite rate of around 40% in the standard dosing (arm S).

It is expected that the TTV-guided immunosuppression (arm T) reduces the occurrence of the primary endpoint, and therefore rates between 20% and 30% are assumed to be reasonable.

The non-inferiority margin has been fixed 10% points (see also above). Thus when the sample size in each group is 120, a two-group large-sample normal approximation test of proportions with a one-sided 2.5% significance level will have 90.42% power to reject the null hypothesis

that arm T is inferior to standard arm S (the difference in proportions,  $\pi_1 - \pi_0$ , is 0.1 or farther from zero in the same direction) in favour of the alternative hypothesis arm T is not inferior to arm S, assuming that the expected proportions are 0.3 and 0.4 in arm T and S, respectively (i.e. assuming a better outcome in arm T).

Due to the planned observation period of 9 months and the special patient population, a rather low drop-out rate is expected of about 2-5%. Adjusting for potential drop-outs, the sample size is fixed with 130 patients per group, i.e., 260 in total.

The sample size calculation was performed using N-Query Version 8.6.1.

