### 10.3.3 STATISTICAL ANALYSIS OF THE PRIMARY END POINT

The occurrence of the primary composite endpoint will be presented per treatment group as absolute numbers and percentages. The difference of the occurrence of the primary endpoint between the two treatment groups and a two-sided 95% confidence interval will be calculated.

Non-inferiority will be concluded if the upper limit of a two-sided 95% confidence interval for the difference in proportion of patients at month 9 after randomization (= Visit 7; post-transplant month 12) between the two treatment arms is less than 10% points. Superiority will be concluded if the confidence interval excludes 0.

As additional sensitivity analyses confidence intervals will be calculated being adjusted for study stratifications (such as centers) using Cochrane-Mantel-Haenszel weights. Also logistic regression models will be used using additional factors (such as sex) and covariate (such as age at randomization).

To explore the composite endpoint further, it will be also be analyzed as time-to-event endpoint considering the time from randomization till time of first event. We will visualize these data by presenting Kaplan-Meier curves for each treatment arm. Furthermore, Cox-regressions models will be performed adjusting for the same factors and covariates as used in the logistic regression models.

To address the repetitive nature of the events used in the definition of the primary endpoint, we will also perform supportive analyses for recurrent event data. We will fit a negative Binomial regression model for the events of the composite endpoints accounting for the time a patient is under risk. Furthermore, we will perform the counting process model of Andersen-Gill and frailty models.

To assess the impact of the individual components of the composite endpoints, each component will be analyzed descriptively (see description for secondary endpoints).

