#### 10.3.5 MULTIPLE TESTING

For the primary endpoint we will use a hierarchical testing procedure. This means first we will test the non-inferiority hypothesis at a one-sided alpha of 2.5%. After non-inferiority can be demonstrated, superiority will be tested also using a one-sided alpha of 2.5%.

The secondary endpoints include the components of the primary outcome and are needed to support the interpretation of the potential effects in the primary endpoint. The tests for this comparisons would require larger sample sizes to achieve the required power. This was the reason why a composite endpoint has been chosen and these analyses are considered supportive only without further multiplicity correction.

For the analyses of all secondary endpoints two-sided p-values and two-sided 95%-confidence intervals will be reported.

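### Section 3.5 claims sufficient power for superiority at any difference larger than 40% versus 30%, but the design reaches 80% power only at a reduction of about 17 points

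*Protocol*

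**What the plan says.** Section 3.5 sets 260 patients (130 per arm) and gives power above 90% for non-inferiority, assuming a decrease in the primary composite from 40% to 30% at one-sided 2.5%. The next sentence reads: "If the differences are larger, there is also sufficient power to demonstrate superiority". It then refers to section 10 for details.

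Section 10.2 takes about 40% in the standard arm and says of arm T that "rates between 20% and 30% are assumed to be reasonable". It states one power figure, 90.42% for non-inferiority with 120 per arm, "assuming that the expected proportions are 0.3 and 0.4 in arm T and S, respectively". On the margin it says: "The non-inferiority margin has been fixed 10% points". The step from 120 to 130 per arm covers an expected drop-out of 2-5%.

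Superiority is the second step of the hierarchy. Under section 10.3.5, once non-inferiority is shown, "superiority will be tested also using a one-sided alpha of 2.5" per cent. No power for superiority is given anywhere in the protocol.

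**The concern.** The only difference named before the sentence in section 3.5 is the fall from 40% to 30%. The plain reading is therefore that any reduction beyond 10 points gives adequate power for superiority. A non-inferiority design gains the margin as extra distance from the null: at 40% versus 30% with a 10-point margin, the test has 20 points to work with. The superiority test has only the true difference itself, so good power for the first test says little about the second.

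Superiority is a planned confirmatory step, and section 1.3.1 anticipates a reduction from 40% to 30%. If the true benefit is in the lower part of the planning range, a non-significant superiority test is a likely result even though the intervention works. A reader who relied on section 3.5 could give that result more weight than it can bear.

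**Working it through.** **Inputs.** Control rate pS = 0.40, arm T rate pT from 0.20 to 0.30, margin 0.10, 120 per arm for the power statement and 130 randomised per arm (all section 10.2); one-sided 2.5%, z = 1.96 (sections 10.2 and 10.3.5).

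**Step 1: reproduce the protocol's figure.** Normal approximation with unpooled variance:

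SE = √{[pT(1−pT) + pS(1−pS)]/n} = √{(0.21 + 0.24)/120} = 0.06124

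Power for non-inferiority = Φ((0.10 + 0.40 − 0.30)/0.06124 − 1.96) = Φ(3.266 − 1.96) = 0.9042

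This is the stated 90.42%. Pooled variance would give 90.11%, so the unpooled form is the one that matches.

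**Step 2: the same formula for superiority.** The margin drops out:

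Power = Φ((pS − pT)/SE − 1.96)

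For example, with pT = 0.25 and n = 120, SE = √{(0.1875 + 0.24)/120} = 0.05969, 0.15/0.05969 = 2.513, and power = Φ(0.553) = 0.71.

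| Arm T rate | Reduction (points) | 120 per arm | 130 per arm, all complete |
|---|---|---|---|
| 30% | 10 | 37% | 40% |
| 29% | 11 | 44% | 47% |
| 28% | 12 | 51% | 54% |
| 25% | 15 | 71% | 74% |
| 24% | 16 | 77% | 80% |
| 23% | 17 | 82% | 85% |
| 20% | 20 | 93% | 95% |

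A pooled-variance version is lower by at most about 1 point.

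**Step 3: reduction needed, with control at 40%.**

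| Target power | 120 per arm | 130 per arm, all complete |
|---|---|---|
| 80% | 16.6 points (arm T about 23.4%) | 16.0 points |
| 90% | 18.9 points (arm T about 21.1%) | 18.2 points |

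**Step 4: the missing-data rule.** Section 10.3.7 counts missing values as failures in the primary analysis. With 130 per arm and a share d missing in each arm, a rate p becomes p(1−d) + d. At d = 5%, the upper end of the drop-out range:

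- control: 0.40 × 0.95 + 0.05 = 0.43
- arm T at 30%, 25% and 20%: 0.335, 0.2875 and 0.24

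Power for superiority is then about 35%, 68% and 91%, and 80% power needs a true reduction of about 17.2 points. With 2% missing it needs about 16.4 points. The 120-per-arm figures are therefore a fair summary; figures for 130 complete patients per arm would be too favourable.

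**The case against.** The strongest reply is about wording. The sentence gives neither a threshold nor a definition of sufficient, and it can be read loosely as referring to differences that are larger by enough. On that reading it is true at an arm T rate of 20%, where power is about 93%. The protocol sets no target power for superiority, so 80% is a benchmark brought in from outside. The primary objective is non-inferiority, the sample size rests on that alone, and low superiority power at the planning effect is ordinary in such a trial. The result will also be reported with a 95% confidence interval, which shows the imprecision.

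Much of this stands, and it limits the point to an overstatement of minor weight. It does not rescue the sentence. The only antecedent is the 10-point decrease, and at 11 or 12 points power is about 44% or 51%, which no usual standard calls sufficient. Replacing 80% by the 90% level that the protocol uses for non-inferiority makes the gap wider.

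A reader might also infer a fault in two neighbouring passages. Section 10.1 says "If non-inferiority is reached, the study will demonstrate superiority of TTV-guided immunosuppression", which could be taken as a promise, and section 10.3.3 says "Superiority will be concluded if the confidence interval excludes 0", which names no direction. The documents do not support either inference. The sentence in 10.1 goes on to say that this is done by a hypothesis test, its alternative fixes the direction as a lower rate in arm T, and section 10.3.5 makes the test one-sided and conditional on non-inferiority. No result depends on rewording either passage.

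**Conclusion.** The power property stated in section 3.5 is overstated as written. On the protocol's own basis, superiority power over the planning range runs from about 37% to about 93%, and it passes 80% only when the true reduction is about 16.6 points or more. The unqualified statement holds only near the favourable end of that range.

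This rests on a control rate of 40%, the unpooled normal approximation that reproduces 90.42%, and 80% as the conventional minimum.

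It would go too far to say that the sentence is false everywhere or that the trial is too small for its purpose. It holds near 20% in arm T, and the non-inferiority calculation is correct. Nor can one say how likely the shortfall is, since section 10.2 gives no weights to rates within 20% to 30%. Sample size, non-inferiority power and type I error are untouched. Severity: minor.

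**What to change.** Delete the sentence on superiority in section 3.5 and replace it with a reference to section 10.2. There, add wording such as:

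> With 120 evaluable patients per arm, power for superiority is about 37%, 71% and 93% for arm T rates of 30%, 25% and 20%; 80% power requires a true reduction of about 17 points.

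If the sponsor prefers the randomised number, the figures for 130 per arm with 5% missing counted as failures are about 35%, 68% and 91%, again with 80% power at about 17 points. Whichever basis is used should be named.

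The cost is two sentences and a less favourable stated property. No patients, procedures or analyses change, and sections 10.1 and 10.3.3 can stay as they are.

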### 3.6 SUBJECT RECRUITMENT

Recruitment and trial entry is detailed in Figure 1. All consecutive adult recipients of a kidney allograft will be subjected to screening within the first two week after transplantation at the inpatient ward by the study team (study visit -3) and entered in the screening log. If baseline inclusion criteria are met (e.g. tacrolimus-based immunosuppression) and no baseline exclusion criteria are present (e.g. immunologic high risk, active participation in another clinical trial, any state that excludes adherence with the trial protocol, inability to perform study visits at the trial centre) informed consent will be obtained and TTV will be quantified. TTV will then be assessed in month 2 and 3 after transplantation at routine study visits.

### 3.7 TIME SCHEDULE

#### **Trial Flow and Design**

The trial flow and design is detailed in Figure 1 and Figure 2. Patients will meet the study team again at the outpatient clinic in month 4 after transplantation at a routine visit. If all inclusion criteria are met and no exclusion criteria are present participants will be enrolled into the clinical trial and randomized (study visit 1). TAC dose will be adjusted according to TTV-guided TAC trough level target or routine centre TAC trough level target. Participants will visit the outpatient

clinic every 6 weeks following the same procedure up to and including month 12 after transplantation (study visit 6). Follow-up will be performed until month 13 post-transplantation (study visit 7).

#### End of trial

The end of trial is last visit of last patient (LPLV).

**Figure 1 Trial Flow.**

[figure not shown]

\* Other procedures: see 'trial procedures'

**Figure 2 Trial Design.**

## TRANSPLANTATION (TX)

[figure not shown]

### 3.8 REQUIREMENTS FOR TRIAL SITES AND INVESTIGATORS

All clinical/recruitment centres are university-based tertiary care centres with a high-volume kidney transplant unit. The local PIs at the participating trial sites are internationally recognised scientists in the field of kidney transplantation with a track record of successful conduction of interventional clinical trials. At each centre, appropriately trained medical staff will be available to provide the necessary standard of care for trial participants and to perform medical care specific to the trial and beyond. The trial sites have a local laboratory or cooperate contractually with external service providers in order to be able to perform the laboratory diagnostics required for the trial in a qualified manner. Current quality certificates or adequate certification of other established quality control measures are provided to the sponsor to demonstrate that the investigations are properly performed during the trial period. The trial sites have Internet access in order to use web-based randomization and data entry via eCRF.

Due to their combination of fundamental virological research, applied medical-virological research, viral diagnostics and university and postgraduate teaching, the participating laboratories are centres of excellence for all current aspects of medically oriented virology. The participating trial sites have adequate human resources throughout the trial. The personnel involved in the clinical trial are qualified in accordance with the quality standards of "good clinical practice".

The investigator is responsible for selecting and assembling the members of the trial team (especially the medical staff) in accordance with the requirements of this protocol. In addition, the investigator is responsible for the training and supervision of the trial team and for providing all necessary information.

## 4 POPULATION OF TRIAL SUBJECTS

### 4.1 DESCRIPTION OF THE TRIAL POPULATION

#### **Gender and age distribution**

The trial is expected to be safe for both men and women, and differences in treatment effects between the sexes are unlikely. However, gender and sex dimensions are important factors in the proposed project and have been taken into account at various stages of the trial.

- At the stage of trial design, we considered the association between sex and TTV level, organ rejection and medical adherence: female sex is associated with lower TTV levels and lower rates of rejection and non-adherence. Analysis of the DSMB will stratify according to sex for early detection of sex related risks. Baseline variables and follow-up data known to be influenced by sex and gender will be collected. The study is designed as a mixed-sex study with equal sex distribution among the participants in order to reflect the composition of the group of patients likely to be treated with the strategy under investigation. An equal sex distribution within treatment arms will be guaranteed by appropriate randomization allocation and concealment.

- At the stage of analysis, data will be analysed separately for each sex and possible effect modifications will be considered. Likewise, factors that interact with sex/gender (as explored during statistical evaluation of the results) will be included. The study is not powered to analyse the outcome stratified for sex/gender as a subgroup.

- At the stage of dissemination, results will be displayed according to sex/gender and differences between the sexes/genders will be reported. Implications for clinical practice or further research concerning sex/gender will be emphasised.

#### **Dependent persons**

Persons dependent on the sponsor, investigator or medical staff of the trial team must not be included.

#### **Special protection**

Members of particularly vulnerable groups such as:

- underage persons,
- pregnant and breastfeeding women,
- adults who are not able to recognise the nature, significance and scope of the clinical trial and to orient their will accordingly,
- persons who are unable to give informed consent,
- persons who are accommodated in an institution by court or official order

will not be included.

Immunological high-risk patients will also be excluded.

### 4.2 INCLUSION CRITERIA

1. Recipient of a kidney allograft
2. Adult ( $\geq 18$  years of age)
3. Post day 93 following transplantation
4. TAC-based immunosuppression

5. Standard target TAC trough level (as defined by local centre; might exclude patients with e.g. a lung transplantation or *de novo* DSA or thrombotic microangiopathy [TMA] if the centre applies non-standard TAC trough levels in these circumstances)
6. Written informed consent

### 4.3 EXCLUSION CRITERIA

1. HLA incompatible transplantation (as defined by local centre; e.g. preformed DSA and/or crossmatch conversion)
2. ABO incompatible transplantation (as defined by local centre; e.g. relevant ABO incompatible blood group combination)
3. Combined transplantation
4. History of HIV or active Hep B/C infection
5. Donor with history of HIV or active Hep B/C infection
6. TTV load always below  $4.6 \log_{10}$  c/mL during screening phase
7. No stable TAC trough levels achieved during screening phase (as defined by local centre)
8. Hypersensitivity to TAC or other macrolides and hypersensitivity to any excipients
9. Cyclosporine, mTor inhibitor or Co-stimulation blocker based immunosuppression
10. No standard immunosuppression according to local centre definition; e.g. necessity of significant additional long term immunosuppression or immune modulation (e.g. disease modifying agents in autoimmune disease or immune modulators for cancer)
11. Treatment with T-cell depleting drugs within 2 months before the randomization (e.g. anti-thymocyte globulin)
12. Current infection or allograft rejection as defined by the primary end-point
13. Biopsy proven antibody mediated rejection (ABMR) or BK virus PCR  $\geq 10^4$  c/ml (or corresponding U/mL) in the blood until randomisation
14. Unstable graft function: eGFR  $< 25$  mL/min/1.73m^2 (this limit might be ignored if creatinine clearance is  $> 25$  mL/min/1.73m^2) or rapid and relevant eGFR decline (as defined by local centre), urinary protein/ creatinine ratio  $> 2000$  mg/g, or rapid and relevant increase (as defined by local centre).
15. Advanced liver failure (CHILD-Pugh score C)
16. History of malignancy other than squamous cell carcinoma or basal cell carcinoma of the skin or carcinoma in situ or adenoma of the colon within the last 5 years unless in complete remission since at least 3 years
17. Leukopenia  $< 2000/\text{mm}^3$  or neutropenia  $< 1000/\text{mm}^3$
18. Unstable angina, cardiac decompensation with the necessity of inpatient treatment
19. Severe tremor (as defined by local centre) due to TAC
20. Inability to perform study visits at the trial centre
21. Any state that excludes adherence with the trial protocol, such as serious medical or psychiatric illness, language barrier, alcohol or illicit substance abuse or non-adherence
22. Addictions or other illnesses that do not allow the person concerned to assess the nature and extent of the clinical trial and its possible consequences
23. Simultaneous participation in another interventional clinical trial
24. Pregnant or breastfeeding women
25. Women of childbearing potential, except women who meet one of the following criteria:
  - a) post-menopausal (12 months natural amenorrhoea)

- b) postoperative (6 weeks after bilateral ovariectomy with or without hysterectomy, bilateral salpingectomy)
- c) regular and correct use of a contraceptive method with an Pearl Index < 1% per year
- d) sexual abstinence
- e) Vasectomy of the partner

